#### Pilot project

The design of the proposed research project is based on the pilot analysis that was carried out in the Comprehensive Stroke Centre in the Hospital in Ceske Budejovice, where data from a total of 109 patients with suspected stroke were evaluated. These patients underwent multimodal CT examinations (NCCT, multiphase CTA, and CTP) as per the stroke protocol. MRI examination DWI/FLAIR mismatch was selectively indicated as determined by the clinical context.

Based on the performed examinations, stroke was detected in 72 cases, and SM were detected in 37 cases (34%) (see Tables 2, 3).

**Table 2 tab2:** Demographic data of patients in a pilot project.

Suspected stroke		109 patients	
Stroke	66%	Stroke mimics	34%
Male	53%	Male	51%
Female	47%	Female	49%
Age (average value)	71.1 ± 15.5	Age (average’)	67.9 ± 15.5

**Table 3 tab3:** Detection of stroke mimics.

Stroke mimics	37	34.0%
Metabolic and/or cardiovascular disorder	7	6.4%
Seizures	5	4.6%
Functional disorder	3	2.8%
Trauma	3	2.8%
Neuropsychiatric manifestations	3	2.8%
Drug intoxication	2	1.8%
Bell’s palsy	1	0.9%
Vestibular syndrome	1	0.9%
Migraine	1	0.9%
Spondylogenic symptom	1	0.9%
Inconclusive or unexplained cause	10	9.2%

Seven patients (6.4%) had symptoms caused by a metabolic disorder and/or a cardiovascular disorder; five patients (4.6%) had symptoms of seizures; and three patients in each group (2.8%) had symptoms of functional disorder, trauma, and neuropsychiatric manifestations (see Table 2). The SM diagnosis was determined in the cases of drug intoxication in two patients (1.8%) and Bell’s palsy, vestibular syndrome, migraine, and spondylogenic symptoms in one patient. An inconclusive or unexplained cause of health complications was found in a total of 10 (9.2%) cases.

## Discussion

This project aims to clarify stroke and SM symptoms in hospital care, potentially modifying care provision. It could substantiate international publications and validate the role of multimodal CT in stroke and SM diagnosis.

It is common knowledge that the examination with the highest sensitivity and specificity for the diagnosis of ischaemic stroke is the MR examination of the brain (16). MR examination has numerous contraindications, and as part of an acute diagnosis, stroke is not routinely used. On the other hand, multimodal CT examinations (including non-contrast head CT (NCCT), head and neck CT angiography (CTA), and CTP) may play a significant role in providing accurate information about brain pathology in a short period of time. NCCT (17) and head and neck CTA, which are commonly used for the detection of large vessel occlusion, remain the gold standard in neuroimaging diagnostics in the case of suspected stroke, whilst CTP may play an important role in the diagnosis of SM. However, CTP is currently not a standard part of the diagnostic procedure in most stroke centres. Most patients with SM exhibited discordant clinical findings when compared to CTP imaging. Normal or entirely discordant Tmax of 6 s abnormalities are more common in patients with SM. Therefore, CTP could be crucial when deciding on the use of intravenous thrombolytic therapy (4). The sensitivity of acute NCCT examination for the diagnosis of ischaemic stroke is low (33%) (5).

The outcome of this project is based on the evaluation that the combination of NCCT, CTA, and CTP is superior to NCCT alone or the combination of NCCT and CTA in the diagnosis of SM in patients with acute neurological deficits. The final diagnosis of SM will be determined based on a unique combination of knowledge of clinical data and multimodal CT and MRI results.

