**Methodology:**

In this study, we will include 3,000 patients consecutively admitted to the comprehensive stroke centres with a diagnosis of suspected stroke. On the basis of clinical parameters and the results of multimodal CT and magnetic resonance imaging (MRI), the diagnosis of stroke and SM will be established. To clarify the significance of the use of the multimodal CT scan, the analysis will include a comparison of the blinded results for each imaging scan performed by radiologists and AI technology and a comparison of the initial and final diagnosis of the enrolled patients. Based on our results, we will compare the economic indicators and costs that would be saved by not providing inadequate treatment to patients with SM.

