## Overall goals of the project

This project aims to optimise hospital diagnostics for stroke and SM symptoms, focusing on the specificity and sensitivity of multimodal brain imaging compared to conventional imaging. The specific goals of the study include evaluating diagnostic outcomes between blinded radiologists/AI technology and clinical diagnosis as well as comparing economic indicators to identify potential savings from avoiding unnecessary treatments.

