### Statistic analysis

A minimum of 718 patients is required to demonstrate significant differences between diagnostic approaches. The analysis involves appropriate statistical tests and logistic regression to assess factors influencing clinical diagnosis. It is expected that the total number of enrolled patients will be 3,000 in order to ensure the availability of all established parameters and, particularly, the relevance of the data obtained. The sample size was determined using the proportional data from the pilot project (*p* = 0.34 for the observation group and a desired effect of at least 10%), 5% significance level, and 80% power.

Numerical variables are presented as medians and ranges or interquartile ranges. Categorical variables are presented as absolute and relative frequencies. The association between demographic, clinical, or radiographic variables and the clinical diagnosis (stroke and stroke mimic) is analysed using appropriate statistical tests—Mann–Whitney test, chi-squared test of independence for contingency tables, or other statistical tests, if necessary. Eventually, logistic regression can be used for analysing the effect of multiple factors on the clinical diagnosis.

The diagnostic accuracy of applied diagnostic methods will be evaluated using common measurements, including accuracy, sensitivity, specificity, positive predictive value, and negative predictive value. The characteristics will be reported with their confidence intervals. The significance level is set to 5%, and statistical analyses will be performed using appropriate statistical software (R, STATA) with maximum available data.

The pharmacoeconomic analysis will include a health technology assessment (HTA) to calculate the potential value of innovation at an early stage, analysing not only the QoL of patients but also the costs associated with the treatment of stroke and SM. The calculation of costs is based on the average cost of thrombolysis and its associated treatment, representing the incremental cost (IC). Economic evaluation is organised as a test of dominance of improved results (meaning fewer complications associated with the administration of thrombolysis) and lower costs.

To calculate the overall benefit, the value of the QoL and the specific parameter of the quality-adjusted life years (QALY) set for the Czech Republic will be used.

The results will be reported as expected ICs and effects (E) expressed in quality-adjusted years of life (QALY).

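### The superiority statement for adding CTP does not fix which comparator, or which of sensitivity and specificity, decides it

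*Protocol article*

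**What the plan says.** - **Hypothesis.** The Discussion rests the project's outcome on this statement: "combination of NCCT, CTA, and CTP is superior to NCCT alone or the combination of NCCT and CTA in the diagnosis of SM". The population is people presenting with an acute deficit.
- **Goals.** The Overall goals section puts the focus on the "specificity and sensitivity of multimodal brain imaging compared to conventional imaging"; it does not define conventional imaging. The Aim in the Abstract also names sensitivity and specificity together and ranks neither.
- **Analysis.** The Statistic analysis section lists "common measurements, including accuracy, sensitivity, specificity, positive predictive value, and negative predictive value", to be given with confidence intervals. None is marked as deciding, and no test between CT combinations is named.
- **Size.** The same section states: "A minimum of 718 patients is required to demonstrate significant differences between diagnostic approaches". This is tied to a "5% significance level, and 80% power".
- **Standard of care.** The Abstract and the Discussion both describe NCCT together with CTA as the present gold standard. The Discussion gives acute NCCT a sensitivity of 33% for ischaemic stroke.
- **Readers.** The Abstract plans a "comparison of the blinded results for each imaging scan performed by radiologists and AI technology". The section on analysing the CT and MRI examinations sets the blinded radiologist's evaluation beside the AI evaluation.

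**The concern.** The article asks what CTP contributes, but its superiority sentence can be satisfied by a result that does not answer that question. NCCT alone differs from the three-component examination by CTA and by CTP. If CTA helps and CTP adds nothing, the three-component set still beats NCCT alone. Taken literally, the sentence then allows a conclusion in favour of CTP.

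The second gap is the measure. Sensitivity and specificity for SM can move in opposite directions when a test is added. If the deciding measure is not fixed, a gain on one could be called superiority while the other worsens. This matters because the Discussion links CTP to the decision on thrombolysis: a gain in SM sensitivity bought with strokes labelled as mimics would be a consequential error.

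**Working it through.** **1. Does the sample size identify the contrast?** The inputs in Statistic analysis are p = 0.34, an effect of 10%, 5% significance and 80% power; the stated result is 718.

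- Two independent groups, two-sided, 1:1: 0.34 v 0.44 gives 746 in total; 0.34 v 0.24 gives 646.
- Single-variance form: 2 × 0.34 × 0.66 × (1.960 + 0.842)² / 0.10² ≈ 352.3, so 353 per group and 706 in total, 1.7% below 718.
- 0.34 v 0.24 with 2:1 allocation gives 714.

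So 718 is reproduced approximately, and only with a formula or allocation that the text does not state. The 0.34 is the SM share in the pilot (37/109 = 33.9%), not the sensitivity or specificity of any CT combination. The calculation therefore points to no comparator and no measure.

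**2. What each comparator isolates.**

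| Contrast with NCCT+CTA+CTP | Components that differ | Answers what CTP adds? |
|---|---|---|
| NCCT alone | CTA and CTP | No |
| NCCT+CTA | CTP only | Yes |

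**3. Sensitivity against specificity.** Suppose patients with negative NCCT and CTA are presumed to have stroke, and a negative or discordant CTP relabels them as SM. SM sensitivity can then only rise or stay the same, and SM specificity can only fall or stay the same. If they are presumed SM and a positive CTP relabels them as stroke, the reverse holds.

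Illustration with 3,000 patients and 34% SM: 1,020 SM and 1,980 strokes. The relabelling rates are assumed, not taken from the article: 20% of SM relabelled correctly and 10% of strokes relabelled wrongly. With all changes in one direction, the McNemar statistic is the square root of the number changed.

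- SM sensitivity: 0.20 × 1,020 = 204 gained; z = √204 = +14.3.
- SM specificity: 0.10 × 1,980 = 198 lost; z = −√198 = −14.1.
- Accuracy: (204 − 198)/3,000 = +0.2 points; z = 6/√402 = 0.30.

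The same data read as better, worse or unchanged according to the measure chosen.

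**4. Chance of a false favourable result.** Assume two-sided 5% tests, so 2.5% in the favourable direction, one reader, and no true difference between the three combinations.

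- One measure, two comparators that share the three-component read: 4.5% at correlation 0.5.
- Sensitivity and specificity rest on different patients, so they are treated as independent: 1 − (1 − 0.045)² = 8.8%.
- Ceiling if all four contrasts were independent: 1 − 0.975⁴ = 9.6%.

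A simulation of paired reads with McNemar statistics agrees. It used 34% SM, an assumed sensitivity and specificity of 0.70, and assumed latent correlations between combinations as shown.

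| N | Correlation | One contrast | Sensitivity, two comparators | Sensitivity or specificity, two comparators |
|---|---|---|---|---|
| 718 | 0.3 | 2.1% | 4.0% | 8.5% |
| 718 | 0.5 | 2.4% | 4.6% | 8.9% |
| 718 | 0.8 | 2.0% | 3.9% | 8.5% |
| 3,000 | 0.3 | 1.9% | 4.0% | 7.6% |
| 3,000 | 0.5 | 3.1% | 5.5% | 9.8% |
| 3,000 | 0.8 | 2.2% | 4.5% | 9.6% |

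There were 2,500 runs per row at 718 and 1,200 at 3,000. At 1,200 runs the standard error near 9% is √(0.09 × 0.91/1,200) = 0.8 points, so the differences between rows are largely noise.

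**The case against.** **It is an article, and a statistical analysis plan may exist.** Ranking of endpoints and multiplicity rules are commonly left to that plan, so their absence here is not a fault. This stands. The point is confined to a hypothesis that the article does state, and states as an alternative between two comparators. An analysis plan would have to choose between its readings.

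**'Superior to A or B' can mean superior to each.** That is ordinary usage and may be what was meant. With the gold-standard remarks, it even suggests that NCCT plus CTA is the intended comparator. But the text does not say so, and conventional imaging is left undefined.

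**A reader might infer much more:** two comparators × five measures × two readers = 20 contrasts, each tested at 5%, with a 64% chance of some false significant result if independent (1 − 0.95²⁰), or 42% at correlation 0.5. The documents do not support this:

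- The Aim and the Overall goals narrow the focus to sensitivity and specificity.
- AI is set beside the radiologist for comparison, not offered as a second route to success.
- The 5% level is a general setting, and the accuracy measures are to be reported with confidence intervals.
- Those two percentages also count significantly worse results, which nobody could call superior.

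**The error-rate model is limited.** It assumes that CTA as well as CTP adds nothing. If CTA truly helps, a win over NCCT alone is not a false positive but a true result credited to the wrong component. The model also lets reads change in both directions, unlike the one-way relabelling in the illustration. Both remarks are fair. Under this null, significant results in opposite directions are rare (about 2% even across all 20 contrasts), so the conflict matters only if there is a real trade-off.

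**Reporting both measures would expose a loss of specificity.** It would, but the article would still not say whether that loss defeats the claim.

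**Conclusion.** The point holds, limited to the ambiguous hypothesis. As written, a win over NCCT alone, or on only one of SM sensitivity and specificity, could carry a claim about CTP that the data do not support. The comparator argument needs no numerical assumption. The possible conflict between measures depends on how CTP changes the label, and its size in the illustration depends on the assumed rates.

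The chance of a false favourable result is about 8 to 10% against 2.5%. This assumes two-sided 5% tests, one reader, two measures, two comparators and no true difference. With one measure and two comparators it is about 4 to 6%. The data remain fully usable; what needs correcting before analysis is the rule by which the headline claim is judged.

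**What to change.** Before the data are analysed:

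1. In the Discussion's superiority sentence, drop NCCT alone so that NCCT plus CTA is the only comparator.
2. In Statistic analysis, name one deciding within-patient contrast: NCCT+CTA+CTP versus NCCT+CTA, blinded radiologist read, SM as the target condition, analysed as paired data (for example by McNemar's test).
3. Judge it on both measures together. Claim superiority on SM sensitivity only if the confidence interval for the paired difference in SM specificity also rules out a loss beyond a limit that the investigators set in advance. Since both conditions must hold, no split of the significance level is needed, and the false-claim rate on sensitivity stays at or below 2.5%.
4. Report NCCT alone, the AI reads, overall accuracy, PPV and NPV as secondary, with confidence intervals and no superiority claim.

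The cost is a few sentences. No extra patients or scans are needed, since the stroke protocol gives every patient all three CT components; no extra reads are needed if each component is read separately, as the Abstract suggests. The downside is that a win on one measure only, or only over NCCT alone, can no longer be called superiority, and the specificity limit has to be agreed. The size of that limit and the exact ranking of the secondary measures are for the investigators to choose.

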## Conclusion

The project’s anticipated outcome is an optimised diagnostic procedure, reducing the risk of inadequate treatment for suspected stroke patients. The applied research may yield health and socioeconomic benefits, improving healthcare provision and reducing costs.

## Ethics statement

The studies involving humans were approved by Ethics Committee at the University Hospital in Ostrava, No. 503/2022, 23.6.2022; Ethics Committee at the Hospital in České Budějovice, No. 109/22, 24.6.2022. The studies were conducted in accordance with the local legislation and institutional requirements. The participants provided their written informed consent to participate in this study.
